### 3. PURPOSE AND DESIGN OF THE RESEARCH

#### A7. Select the appropriate methodology description for this research. *Please tick all that apply:*

- ☐ Case series/ case note review
- ☐ Case control
- ☐ Cohort observation
- ☐ Controlled trial without randomisation
- ☐ Cross-sectional study
- ☐ Database analysis
- ☐ Epidemiology
- ☐ Feasibility/ pilot study
- ☒ Laboratory study
- ☐ Metanalysis
- ☐ Qualitative research
- ☐ Questionnaire, interview or observation study
- ☒ Randomised controlled trial
- ☐ Other (please specify)

#### A10. What is the principal research question/objective? *Please put this in language comprehensible to a lay person.*

Objective 1 (part A): To investigate sex differences in the muscle damage response to acute resistance exercise performed with heavy or lighter weights.

Objective 2 (part B): To investigate the impact of milk protein ingestion on resistance exercise-induced muscle damage and recovery in females.

#### A11. What are the secondary research questions/objectives if applicable? *Please put this in language comprehensible to*

*a lay person.*

To investigate whether a relationship exists between exercise-induced muscle damage and total lean body mass (muscle mass)

To conduct a precision assessment of dual energy X-ray absorptiometry for measuring whole body composition (part A)

**A12. What is the scientific justification for the research? Please put this in language comprehensible to a lay person.**

Unaccustomed resistance exercise can cause damage to muscle fibres. Subsequently, individuals may experience muscle soreness and reduced muscle function - such as loss of strength, power, and flexibility – for several days after the exercise bout. This means that individuals may need longer recovery periods before performing another exercise bout, and their performance may be impaired. Further, muscle soreness may reduce the desire to engage in subsequent exercise bouts, particularly in individuals unaccustomed to resistance exercise. Over time, this may compromise the gains in muscle mass and strength which can be achieved through repeated bouts of resistance exercise, i.e. training. Therefore, strategies aiming to reduce the severity of exercise-induced muscle damage and/or to enhance post-exercise recovery processes are advantageous for exercising individuals.

One strategy that may be beneficial in reducing the muscle damage response to resistance exercise is to lift lighter weights, i.e. <70% one repetition maximum (1RM; the maximum weight that can be lifted once). In the past decade, attention has been paid to low-load resistance training owing to its ability to increase muscle mass to the same extent as when heavier weights are lifted ( $\geq 70\%$  1RM). E.g. (Mitchell et al., 2012; Morton et al., 2016; Schoenfeld et al., 2016; Stefanaki et al., 2019). Additionally, individuals engaging in low-load resistance exercise have reported lower ratings of perceived exertion relative to heavier loads (Chen et al., 2020; Mendham et al., 2011). As such, exercising with lighter loads may be the preferred option for those unaccustomed to resistance exercise; elderly populations; and individuals recovering from musculoskeletal injury. Further, low-load resistance exercise may place less mechanical stress on muscle fibres and accordingly, its impact on muscle damage has been investigated. While several studies have reported less severe muscle damage, self-perceived muscle soreness, and functional impairments (such as loss of strength, power, and flexibility) with low-load resistance exercise compared to high-load (Chen et al., 2020; Hasenoeuhl et al., 2017; Mendham et al., 2011; NOSAKA & NEWTON, 2002; Orssatto et al., 2018; P. M. Tiidus & Ianuzzo, 1983), others have found no differences (Draganidis et al., 2013; Güzel et al., 2007; Paschalis et al., 2005; Peake et al., 2006; Uchida et al., 2009). Further, the majority of studies to date have been conducted in young males, with a complete lack of data solely in females.

There is evidence to suggest that males and females may respond differently to resistance exercise, with respect to muscle damage. For instance, some studies have shown greater and more sustained increases in blood markers of muscle damage and inflammation in males than females following resistance exercise (Amorim et al., 2014; Heavens et al., 2014). It has been speculated whether these differences are due to a protective effect of oestrogens (Enns & Tiidus, 2008; Peter M Tiidus, 2003). Therefore, not only is the muscle damage response to heavy vs. lighter resistance exercise inconsistent in males, but it cannot be determined whether females will respond in the same way. Thus, the first objective (part a) of this research is to compare the muscle damage response induced by an acute bout of high- or low- load resistance exercise between males and females.

Another strategy that has shown to reduce exercise-induced muscle damage is the consumption of dietary protein, either as a whole-food source (such as milk) or as a supplement (such as isolated whey protein). It is believed that protein, or rather the amino acids which make up protein, aid the repair or replacement of damaged muscle fibres, then promote growth of the new healthy fibres. Accordingly, research has shown that ingesting protein/amino acids before or after muscle-damaging exercise can alleviate muscle soreness, improve blood markers of muscle damage, and reduce the decline in maximal force and flexibility. In particular, studies have shown that consuming a ~20 g dose of milk protein immediately after (Cockburn et al., 2008) or for several times a day after (Draganidis et al., 2017) resistance exercise improved the recovery time of muscle soreness and maximum force, and also lowered levels of damage markers in the blood. However, these studies were conducted with male participants who were well-trained in resistance exercise. It is not yet known whether milk protein effectively reduces exercise-induced muscle damage in untrained females. Therefore, the second objective (part b) of this research is to investigate the impact of milk protein ingestion on exercise-induced muscle damage in untrained females.

**A13. Please summarise your design and methodology. It should be clear exactly what will happen to the research participant, how many times and in what order. Please complete this section in language comprehensible to the lay person. Do not simply reproduce or refer to the protocol. Further guidance is available in the guidance notes.**

OBJECTIVE 1/PART A: This study will employ a randomised parallel groups design, for which 40 healthy participants (20 males and 20 females) aged 18-35 years will be recruited. Prior to the first laboratory visit, prospective participants will have the opportunity to ask questions and gain further information about the study via a video/phone call with the

lead researcher. If willing to participate, participants will be asked to electronically sign a consent form. Female participants will be asked to record their menstrual cycle and inform the lead researcher at the onset of menses – this information will be used to arrange the time of the baseline assessments, as all measures will be conducted during the late follicular phase of the menstrual cycle.

For the first visit, which acts as a familiarisation session, participants will arrive at the laboratory in the morning and be screened for eligibility with a standard health and readiness to exercise questionnaire. Next, participants will be familiarised with the exercise equipment and demonstrated correct form. Then, participants' maximal strength will be estimated through a one repetition maximum (1RM) test on the leg press and leg extension machines. Approximately three days later, participants will return to the laboratory and a baseline assessment of body composition will be conducted using dual energy X-ray absorptiometry (DXA). Two whole-body DXA scans will be conducted in each participant (one immediately following the other after repositioning) to allow for the precision of DXA to be measured. The 1RM test will be repeated on the leg press and leg extension machines for confirmation of maximal strength. Participants will then be randomly assigned to either a low-load (30% 1RM) or high-load (80% 1RM) exercise condition, such that each group will have an equal number of males and females.

Visit three will occur three weeks later. In between visits two and three, participants will be asked to record their habitual diet and activity for three days, which will be used to assess any between-group differences. For each subsequent assessment day, participants will be prescribed a standardised breakfast to consume at home 3 hours prior to attending the laboratory. Otherwise, participants will be instructed to consume their habitual diet and, during each laboratory visit, a 24-hour dietary recall will be conducted to assess any changes in dietary intake. Participants will be instructed to abstain from the use of non-steroidal anti-inflammatory drugs, strenuous exercise, engagement in massage or cryotherapy, and the consumption of alcohol, protein supplements, vitamin and mineral supplements, and ergogenic aids during the study period.

Upon arriving at the laboratory for the third visit (pre), a trained phlebotomist will collect a venous blood sample in three vacutainers; one containing a serum separator (8.5 mL); and two containing no reagent (10 mL) (28.5 mL total). Following blood collection, the participants' limb circumference of the thigh will be measured with a standard measuring tape and their limb range of motion will be assessed with a goniometer. Muscle soreness will be measured by use of a visual analogue scale (VAS) questionnaire while performing a standard bodyweight squat, and the pressure-pain threshold (PPT) test using a standard pressure algometer. Participants will then perform a single bout of resistance exercise at their allocated load intensity, firstly on the leg press and secondly, on the leg extension, separated by five-minutes rest. The exercise protocol will consist of a warm-up set (10 repetitions at 50% of the participants pre-established 1RM), followed by three sets performed to volitional failure (when a full repetition can no longer be completed) at either 30% or 80% 1RM. Two-minutes of rest will be awarded between each set of exercise and the participants will be verbally encouraged throughout.

Immediately following the exercise bout (post), another venous blood sample will be taken (3 x 8.5-10 mL) and the measures of limb circumference, range of motion, and muscle soreness will be repeated. Then, participants will be provided a dairy yoghurt containing 20 g of milk protein to stimulate muscle repair and growth. These four measures (excluding protein consumption) will be repeated during the morning of visits four (+24 h), five (+48 h), six (+72 h), and seven (+168 h). Also, during visits six and seven, the 1RM strength test will be repeated on the leg press and leg extension. Over the experimental period, a total of 171 mL of blood will be collected from each participant. This is the equivalent of ~34 teaspoons and is a common amount obtained during exercise physiology research. The blood samples will be used to analyse serum concentrations of creatine kinase, myoglobin (markers of muscle damage), C-reactive protein, and interleukin-6 (markers of inflammation).

**OBJECTIVE 2/PART B:** This study will employ a randomised parallel groups design, for which 22 healthy females aged 18-35 years will be recruited. Prior to the first laboratory visit, prospective participants will have the opportunity to ask questions and gain further information about the study via a video/phone call with the lead researcher. If willing to participate, participants will be asked to electronically sign a consent form. Participants will be asked to record their menstrual cycle and inform the lead researcher at the onset of menses – this information will be used to arrange the time of the baseline assessments, as all measures will be conducted during the late follicular phase of the menstrual cycle.

For the first visit, which acts as a familiarisation session, participants will arrive at the laboratory in the morning and be screened for eligibility with a standard health and readiness to exercise questionnaire. Next, participants will be familiarised with the exercise equipment and demonstrated correct form. Then, participants' maximal strength will be estimated through a one repetition maximum (1RM) test on the leg press and leg extension machines. Approximately three days later, participants will return to the laboratory and a baseline assessment of body composition will be conducted using dual energy X-ray absorptiometry (DXA). The 1RM test will be repeated on the leg press and leg extension machines for confirmation of maximal strength. Participants will then be randomly assigned to either a protein or placebo group. The protein group will be consuming a whole-food source of milk protein (dairy yoghurt) providing 20 g of milk protein and the placebo group will consume a carbohydrate-based food source that contains the

same amount of calories.

Visit three will occur three weeks later. In between visits two and three, participants will be asked to record their habitual diet and activity for three days, which will be used to assess any between-group differences. For each subsequent assessment day, participants will be prescribed a standardised breakfast that will contain either the protein or placebo product to consume at home 3 hours prior to attending the laboratory. Participants will consume one dose of their allocated supplement in the laboratory after exercise and be given a further two doses to consume at home interspaced by four hours. Therefore, 4 doses of the supplement will be consumed in each 24-hour period for four consecutive days, though on the final testing day, only one dose will be consumed with breakfast (17 doses total). Otherwise, participants will be instructed to consume their habitual diet, and during each laboratory visit a 24-hour dietary recall will be conducted to assess any changes and between-group differences in dietary intake. Participants will also be instructed to abstain from the use of non-steroidal anti-inflammatory drugs, strenuous exercise, engagement in massage or cryotherapy, and the consumption of alcohol, additional protein supplements, vitamin and mineral supplements, and ergogenic aids during the study period.

Upon arriving at the laboratory for the third visit (pre), a trained phlebotomist will collect a venous blood sample in three vacutainers; one containing a serum separator (8.5 mL); and two containing no reagent (10 mL) (28.5 mL total). Following blood collection, the participants' limb circumference of the thigh will be measured with a standard measuring tape and their limb range of motion will be assessed with a goniometer. Muscle soreness will be measured by use of a visual analogue scale (VAS) questionnaire while performing a standard bodyweight squat, and the pressure-pain threshold (PPT) test using a standard pressure algometer. Participants will then perform a single bout of resistance exercise, firstly on the leg press and secondly, on the leg extension, separated by five-minutes rest. The exercise protocol will consist of a warm-up set (10 repetitions at 50% of the participants pre-established 1RM), followed by three sets performed to volitional failure (when a full repetition can no longer be completed) at 80% 1RM. Two-minutes of rest will be awarded between each set of exercise and the participants will be verbally encouraged throughout.

Immediately following the exercise bout (post), another venous blood sample will be taken (3 x 8.5-10 mL) and the measures of limb circumference, range of motion, and muscle soreness will be repeated. Then, participants will consume their allocated dietary supplement (protein or placebo). These procedures will be repeated during the morning of visits four (+24 h), five (+48 h), six (+72 h), and seven (+168 h). Also, during visits six and seven, the 1RM strength test will be repeated on the leg press and leg extension. Over the experimental period, a total of 171 mL of blood will be collected from each participant. This is the equivalent of ~34 teaspoons and is a common amount obtained during exercise physiology research. The blood samples will be used to analyse serum concentrations of creatine kinase, myoglobin (markers of muscle damage), C-reactive protein, and interleukin-6 (markers of inflammation).

**A14-1. In which aspects of the research process have you actively involved, or will you involve, patients, service users, and/or their carers, or members of the public?**

- ☐ Design of the research
- ☐ Management of the research
- ☐ Undertaking the research
- ☐ Analysis of results
- ☐ Dissemination of findings
- ☒ None of the above

*Give details of involvement, or if none please justify the absence of involvement.*

The participants recruited for this study will be healthy, non-active males and females and the study does not involve the development of a clinical or public health intervention. The focus is on basic science and therefore the involvement of the public in the design of the research is not required.

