**A59. What is the sample size for the research? How many participants/samples/data records do you plan to study in**

*total? If there is more than one group, please give further details below.*

Total UK sample size: 62

Total international sample size (including UK):

Total in European Economic Area:

*Further details:*

PART A: 20 males and 20 females

PART B: 22 females

**A60. How was the sample size decided upon?** *If a formal sample size calculation was used, indicate how this was done, giving sufficient information to justify and reproduce the calculation.*

PART A: A statistical power analysis was conducted. It was determined that a sample size of 8 per group was required to have 80% power to detect a between-group difference in muscle strength of 14%, when using a dependent t-test with a 0.05 two-sided significance level. A ~20% drop-out is anticipated, therefore, 10 males and 10 females in both groups will be recruited (n = 40 total).

PART B: A statistical power analysis was conducted. It was determined that a sample size of 9 per group was required to have 80% power to detect a between-group difference in muscle strength of 13%, when using a dependent t-test with a 0.05 two-sided significance level. A ~20% drop-out is anticipated, therefore, a total of 22 females will be recruited.

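### Both parts randomise at visit 2, three weeks before anything depends on the allocation, so losses in that gap, the habitual diet record and the visit 3 'pre' measures all fall after randomisation

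*Protocol*

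**What the plan says.** The sequence is set out in protocol section A13 and is the same in both parts.

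- **Visit 1:** screening, familiarisation and a first 1RM test.
- **Visit 2:** "Approximately three days later, participants will return to the laboratory and a baseline assessment of body composition" is made by DXA, and the 1RM is repeated. Allocation comes at the end of this visit. Part A: "Participants will then be randomly assigned to either a low-load (30% 1RM) or high-load (80% 1RM) exercise condition". Part B: "Participants will then be randomly assigned to either a protein or placebo group".
- **Gap:** "Visit three will occur three weeks later". During it, "In between visits two and three, participants will be asked to record their habitual diet and activity for three days", and this record is to be used to look for differences between the groups.
- **Visit 3:** "Upon arriving at the laboratory for the third visit (pre), a trained phlebotomist will collect a venous blood sample". Thigh circumference, range of motion, VAS soreness and pressure-pain threshold follow, and then the exercise bout.
- **Part B product:** for each assessment day participants are "prescribed a standardised breakfast that will contain either the protein or placebo product", eaten at home three hours before they attend. The first dose is therefore taken on the morning of visit 3.

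Section A57 names exercise-induced change in muscle damage markers as the primary outcome. Section A60 allows for loss from the groups: "A ~20% drop-out is anticipated, therefore, 10 males and 10 females in both groups will be recruited" in Part A, and 22 recruited for 9 per group in Part B. It does not say when the loss is expected. Section A61 has a coin tossed as each eligible participant is identified. The protocol gives no reason for allocating three weeks ahead, and describes neither blinding nor withholding the allocation during the gap.

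**The concern.** Randomisation protects the comparison from the moment of allocation onwards, so it is best done as late as is practical. Here it is done early and nothing is gained. Both Part A loads are percentages of a 1RM already measured for everyone, so nothing has to be prepared in advance.

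Two things are put at risk.

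1. **Losses without outcome data.** The first blood, soreness, range-of-motion and circumference values are those of visit 3. A participant who leaves in the gap has been allocated but has no marker value at any time, and cannot enter an analysis of change in the group to which she or he was randomised. In Part A such losses also disturb the intended equal numbers of each sex per group. No replacement rule is stated, and the plan has little slack: 8 per group in Part A and 9 in Part B after drop-out.

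2. **Baseline information collected after allocation.** The diet and activity record is meant to describe habitual behaviour, but it is kept by people who have already been assigned. VAS soreness and pain threshold at visit 3 rest on the participant's own report. One student is responsible for all data collection (project filter, question 9), so the person taking the pain-threshold, goniometer and tape measurements may also know the group.

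**Working it through.** **Timeline, from A13.** Visit 1 is day 0. Visit 2 is at about 3 days. Visit 3 is at 3 + 21 = 24 days. Visit 7 is 168 hours (7 days) after the bout, at 24 + 7 = 31 days. This agrees with the one-month participation in A21.

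- From allocation to last visit: 21 + 7 = 28 days.
- Of these, before the bout: 21/28 = 75%.
- Share of the whole participation lying in the gap: 21/31 = 0.677.

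**The plan's own drop-out figures, from A60.**

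- Part A: 8/(1 − 0.20) = 10 per sex per load; 32/0.80 = 40. This reproduces the stated number. Expected loss: 40 − 32 = 8.
- Part B: 18/0.80 = 22.5 against the stated 22. Expected loss: 22 − 18 = 4 (20% of 22 is 4.4).

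**How much of that loss falls in the gap.** The protocol does not say, so the answer is a range that depends on an assumption.

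| Assumption about timing | Part A (of 8) | Part B (of 4) |
|---|---|---|
| None in the gap | 0 | 0 |
| Equal over the 5 between-visit intervals after allocation (1/5) | 1.6 | 0.8 |
| Even over all 31 days (21/31) | 5.4 | 2.7 |
| Even over the 28 days after allocation (21/28) | 6 | 3 |
| All in the gap | 8 | 4 |

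**Effect of allocating after the gap, without replacement.** If a share s of the loss falls before the new allocation point, Part A randomises 40 − 8s and then loses 8 − 8s. That is 8 of 40 at s = 0, 4 of 36 at s = 0.5 and 0 of 32 at s = 1. Part B randomises 22 − 4s and loses 4 − 4s: 4 of 22, 2 of 20 and 0 of 18. The number of completers does not change. What changes is how many of the losses occur after randomisation.

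**What lies on each side of allocation.**

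- Before: both 1RM tests and DXA.
- After: the three-day diet and activity record, every blood marker, circumference, range of motion, VAS and pain threshold, the bout and the supplement.
- In Part B, as worded, the 'pre' measures follow the first dose as well as the allocation. The total of 17 doses agrees with this: 4 a day for 4 days plus 1.

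**The case against.** The strongest reply is that the order is clear but its consequences are not documented. Four parts of that reply deserve weight.

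- **Timing of drop-out.** A reader might infer that most of the expected drop-out falls in the gap, since the gap takes up most of the time after allocation. The protocol does not support this. A60 gives no timing, and the burden is concentrated later: five of the seven visits, all six blood samples and the sets to failure fall in the last week. Losses could cluster there, and zero in the gap is not excluded.
- **Bias needs the allocation to be known.** A reader might also infer that those allocated to the heavier load will leave more often, or that participants will alter their diet or soreness ratings. The protocol says that they are assigned at visit 2, not that they are told. Losses before the bout bias the comparison only if they are related to the allocation. Participants have also done 1RM tests before allocation, and those unwilling to do resistance exercise are excluded. These routes are possible, not shown. What stands is that nothing in the protocol closes them.
- **The key baselines are protected.** 1RM and DXA precede allocation, and strength is the outcome behind both sample sizes. The serum markers are not self-rated. This stands in full.
- **Diet is checked in other ways.** Participants are told to keep to their usual diet, and a 24-hour recall is taken at the laboratory visits. This helps only in part. A18 lists 10 recalls over the two parts, or 5 per part, which matches visits 3 to 7, so these too come after allocation.

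The three-week interval is also not called a run-in in the protocol, and allocating after baseline strength and body composition is not in itself irregular.

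**Conclusion.** The point holds as a weakness of design, not as an error or contradiction. It is certain from A13 that both parts allocate three weeks before the allocation is used, that 21 of the 28 days after allocation precede the bout, and that the diet record and all first marker measures come after allocation with no concealment described. It is also certain that anyone lost in the gap is a randomised participant without marker data.

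The size of the loss is not known. It lies between 0 and 8 of 40 in Part A and between 0 and about 4 of 22 in Part B. The figures of about 5.4 and 2.7 hold only if drop-out is spread evenly over 31 days, which the protocol does not state. Bias in the diet record or the 'pre' ratings requires the allocation to be known during the gap, which the protocol neither states nor rules out. Baseline 1RM and DXA are unaffected.

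The case for change rests on the gap being avoidable: no reason for early allocation is given, and in Part A moving it costs almost nothing.

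**What to change.** **Part A.** In A13, move randomisation from the end of visit 2 to visit 3, after the 'pre' blood, circumference, range-of-motion, VAS and pain-threshold measures and immediately before the bout. Keep the balance by sex. State that anyone who leaves before that point is replaced. Align A61 with this: its coin toss on identifying an eligible participant could be read as allocation as early as visit 1, where eligibility is screened. The cost is wording in two sections, with no added visit or procedure. Each replacement is one more person taken through visits 1 and 2, so A59 should say whether its numbers count people recruited or people randomised.

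**Part B.** Randomise, or at least disclose the allocation, only once the diet and activity record has been returned and the product for the visit 3 breakfast is supplied. The cost is somewhat greater than in Part A. That breakfast is eaten at home and the seven-visit schedule shows no laboratory contact between visits 2 and 3, so a hand-out or delivery must be arranged. The gain is also smaller: the diet record and most of the gap would then precede allocation or its disclosure, but the 'pre' measures would still follow it. If only disclosure is delayed, gap losses remain post-randomisation losses, though participants could not have left because of an allocation they did not know.
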